### Recruitment

We will enroll 600 eligible pregnant smokers to this phase II trial over a 12 month period. This is illustrated in Figure 2 based on existing throughput from local services in the study area and is a conservative time period taking into account smokers not identified or referred and those who decline consent to take part in the incentives trial. We expect high enrollment of eligible smokers and that knowledge of the trial will increase eligible smokers who agree to consider cessation during this pregnancy and consent to take part in the trial.

### Consent and randomization procedure

At least 7 days after the first NSPS contact call, eligible smokers who allow their contact details to be passed on will be contacted by the Helpline to undergo formal consent procedures. Telephone contact will be attempted on three occasions at the time slot preferred by the client - weekday, evening or weekend - after which no further attempts at enrollment will be made. During the consent call potential participants will be fully informed about the nature and relevance of the trial, and exactly what will be involved if they agree to take part. Early in the consent call potential participants will be asked to provide information not asked for at maternity booking including questions measuring level of addiction to nicotine and partner smoking habits. Audio recordings of the consent process will be stored in accordance with Good Clinical Practice guidelines. Eligible smokers who consent to take part in the trial will be sent a written copy of their consent form. Individuals who give informed consent will be enrolled in the trial and randomized. The random allocation will be fed back to the participant. The Helpline adviser cannot influence or predict the random allocation which is integrated into the clinical information system. It will also provide a concealed (not available to the NHS Smokefree Pregnancy Study Helpline adviser during the consent call) random date between 34 and 38 weeks gestation for this pregnancy when the Helpline will contact the participant again to ascertain the primary outcome measure of self reported smoking during the last 8 weeks which will be corroborated by cotinine measurement.

### Baseline (pre-randomization) data collection

#### *Identification and contact*

Patient name, address, full postcode, telephone numbers (home, mobile, office).

Best time to call, best number, estimated date of delivery, name of referrer, General Practitioner name.

#### *Eligibility criteria*

Self reported smoking status at maternity booking, carbon monoxide breath test level at maternity booking, date of carbon monoxide reading, age at first telephone contact, English speaking, gestation at booking, consent, copy of consent form sent.

#### *Smoking addiction level and other*

Fagerstrom questions [24] score out of 10, parity, partner smokes.

### Randomization

Randomization will be embedded within the trial database. The random allocation sequence will be generated by the Robertson Centre for Biostatistics, University of Glasgow (part of the Glasgow Clinical Trials Unit), using the method of randomized permuted blocks, with a block length of 4. In addition, a random date between 34 and 38 weeks gestation for each pregnancy will be generated as the date for primary outcome data collection. Patient details will be entered prior to randomization so that the allocation is concealed from Helpline staff and the client until after the patient has been enrolled in the study and provided baseline information. The participant will be informed of their random allocation group towards the end of the Helpline ‘trial consent’ telephone contact call, but will not be informed of the date when their primary outcome data will be collected.

For a period during trial recruitment an extra consent question will be ‘turned on’ during the consent call asking clients also to consent to being contacted by trial staff for the purposes of one-to-one interviews to fulfill qualitative aspects of this research trial.

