**Figure 2 F2:**
[figure not shown]
**Flow diagram for Cessation in Pregnancy Incentives Trial (CPIT).** Figure 2 projects the flow of pregnant women through the trial over a 12-month period. In the NHS Greater Glasgow & Clyde study area, 15,000 pregnancies are recorded at maternity booking; 5,000 are to smokers, some who conceal their habit, and 3,000 are identified at maternity booking by self-report as current smokers. Their information is routinely passed to NHS Smokefree Pregnancy Services (NSPS) using an automated system. Attempt is made to contact all self reported smokers. We estimate that 500 will not be contactable by NSPS and that 500 will decline permission for their details to be passed to the NHS Smokefree Pregnancy Study Helpline (Study Helpline). Once details have been passed, 500 will not be contactable leaving 1,500 contacted by the Study Helpline. We expect that 600 to 900 will decline consent leaving 600 to 900 who agree to enroll in the study over 12 months. Of these, 300 will be randomly allocated to the intervention group to be offered incentive payments as well as standard care to stop smoking during pregnancy and 300 will be randomly allocated to receive the offer of standard care without incentive payments to quit smoking.

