### NHS Stop Smoking Study Helpline

NHS Stop Smoking Study Helpline will provide call centre services: the consent call for participant enrollment, and the final call to determine the primary outcome (self reported smoking at 34 to 38 weeks gestation).

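### A fixed, published block length of 4 lets Helpline staff who follow the whole sequence deduce up to one third of allocations, so the statement that the adviser cannot predict them is too absolute

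*Protocol article*

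**What the plan says.** The Randomization section of the protocol article states: "The random allocation sequence will be generated by the Robertson Centre for Biostatistics", "using the method of randomized permuted blocks, with a block length of 4". It gives one length, no variation, and names no stratification factor. The Figure 2 legend implies 1:1 allocation: "300 will be randomly allocated to the intervention group" and "300 will be randomly allocated to receive the offer of standard care".

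The section on the NHS Stop Smoking Study Helpline says that this service "will provide call centre services: the consent call for participant enrollment, and the final call to determine the primary outcome". On disclosure, the Randomization section says: "The participant will be informed of their random allocation group towards the end of the Helpline" consent call. It adds that details are entered first, so that "the allocation is concealed from Helpline staff and the client until after the patient has been enrolled in the study" and has given baseline data.

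The section on consent and randomization procedure then claims: "The Helpline adviser cannot influence or predict the random allocation which is integrated into the clinical information system".

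The article does not say whether the block length is withheld from Helpline staff, how many advisers make consent calls, or whether advisers can see each other's allocations.

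**The concern.** Concealing the current allocation is not the same as making it unpredictable. The system hides the next arm until the woman is enrolled, but in a short block of known length the earlier allocations can give the next one away. The Helpline, taken as a unit, learns each allocation as it is made. Embedding the sequence in the database does not help, because the weakness lies in the sequence itself.

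A prediction could matter before consent is complete. Nicotine addiction and partner smoking are asked about early in the consent call, so the adviser holds prognostic information while still explaining the trial. The Figure 2 legend expects 600 to 900 of the 1,500 women contacted to decline (40% to 60%), so the way the trial is presented could affect who enters.

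Events are few. At the assumed 4% control quit rate, 300 women give 12 quitters, and moving three likely quitters into or out of an arm shifts its rate by 3/300, or 1 percentage point. Participants know their arm and the Helpline learns it at the consent call; the blinding described in the Design section covers only the outcome assessor at the follow-up call.

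**Working it through.** The article gives no figure for predictability, so there is none to reproduce. Its power statement is a separate matter and does reproduce: the continuity-corrected formula gives 298 per arm (596 in all) for 4% against 11.4% at 90% power, and 300 per arm (600) for 4% against 10.2% at 80%.

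**Inputs.** Block length 4 (Randomization); 1:1 allocation, hence two of each arm per block (Figure 2 legend); every allocation passes through one Helpline (Helpline section).

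**Observer who knows the block length and boundaries and sees every earlier allocation.** There are six equally likely orderings of AABB.

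| Position in block | Probability that it is certain | Best-guess success |
|---|---|---|
| 1 | 0 | 1/2 |
| 2 | 0 | 2/3 |
| 3 | 1/3 (first two match) | 1/3 + (2/3)(1/2) = 2/3 |
| 4 | 1 | 1 |

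- Certain: (0 + 0 + 1/3 + 1)/4 = 1/3.
- Best guess correct: (1/2 + 2/3 + 2/3 + 1)/4 = 17/24 = 70.8%, against 50% by chance.

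**Several advisers who see only their own calls.** Suppose calls are split at random among k advisers who know the block boundaries but share nothing. An allocation is certain to an adviser only if she took both earlier calls that used up one arm's two places, which has probability 1/k². The certain share is then (1/3)/k². The value of k is an assumption, so a range is shown:

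- k = 1: 33.3%
- k = 2: 8.3%
- k = 3: 3.7%
- k = 4: 2.1%

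A simulation gave the same values to within 0.1 percentage point.

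**Alternatives, for an observer who sees every allocation.** In the mixed schemes the observer knows the set of lengths but not the length of each block. The mixed figures are simulated; those for fixed lengths are exact.

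| Scheme | Certain | Best guess correct |
|---|---|---|
| Fixed 4 | 33.3% | 70.8% |
| Fixed 6 | 25% | 68.3% |
| Fixed 8 | 20% | 66.6% |
| Random 4/6 | about 5.5% | about 69% |
| Random 4/6/8 | about 2.2% | about 68% |
| Simple randomization | 0 | 50% |

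**Cost of simple randomization.** Over n allocations the standard deviation of the difference in arm sizes is √n. Even for all 600 it is √600 = 24.5. A difference of about two standard deviations, 276 against 324, gives an effective size per arm of 2 × 276 × 324/600 = 298, against 300.

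**The case against.** The strongest reply is that one third is a ceiling reached only under conditions the article does not establish. The sequence is made by a separate trials unit and held in the database. Calls are made by an external call centre over daytime, evening and weekend slots, which suggests more than one adviser. Nothing says that these staff know the block length or pool allocations. Consent calls are audio-recorded, and Fagerstrom score and carbon monoxide are recorded before randomization, so gross selection could be detected. This stands, and it is why the figure is given as an upper limit. It does not rescue the flat statement that prediction is impossible, because nothing described in the design rules prediction out.

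A reader might infer more than the document supports:

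- *That a third of allocations are in fact predictable, or that bias has occurred.* The article shows neither.
- *That the sequence is unstratified and, since 199 = 49 × 4 + 3, that the 200th allocation was already fixed.* Absence of strata is only silence in a condensed article. The deduction also needs the arm totals, which are not given. Fixed blocks of 4 within known strata would have the same ceiling.
- *That exactly 401 allocations were exposed, about 134 of them certain.* The count of 199 belongs to 9 June 2012; the number left when the block length became public is unknown.
- *That advisers could time calls to suit the next allocation.* Calls follow the woman's preferred slot, at least 7 days after first contact by the NHS Smokefree Pregnancy Services (NSPS), and no discretion over order is described.
- *That the trial exists to show freedom from selection at consent.* Research question 2 concerns differential follow-up of disaffected control participants.

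**Conclusion.** The concern holds as a design weakness and an overstatement. With a fixed, published block length of 4, up to 1/3 of allocations could be deduced and up to 71% guessed correctly by Helpline staff who know the block length and boundaries and follow the whole sequence. If advisers see only their own calls, the certain share is about 8% for two and 2% for four. Which value applies depends on the number of advisers and what they share, neither of which is stated. The sample size calculation is unaffected. The point merits a change because the remedy is cheap, the arms are open to advisers and participants, and only about 12 control quitters are expected.

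**What to change.** 1. For the allocations still to be made, have the trials unit load a new sequence. One option is randomly varying block lengths (for example 4, 6 and 8), disclosed to neither Helpline nor NSPS staff. This cuts certain allocations to about 2%, but best-guess success only to about 68%, so it removes near-certainty rather than the ability to guess. The other is simple randomization, which restores 50% at the price of a small possible imbalance in arm sizes.
2. Reword the claim in the section on consent and randomization procedure, to say that the current allocation is concealed until the woman is enrolled and has given baseline data.
3. Compare baseline Fagerstrom score and carbon monoxide by arm, before and after the change of sequence. This is a descriptive check; it cannot exclude selection on unmeasured motivation.

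The cost is one new allocation list in the database, a text correction, and a table from data already collected.

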#### *Voucher incentive payments*

Those allocated to the intervention group will be offered financial incentives - Love2Shop vouchers - that can be redeemed in a wide array of UK shops but not used for the purchase of cigarettes or alcohol. The total amount available is £400 if women remain abstinent at each monitoring point. Women will receive incentive payments outlined below:

£50 for attending a face-to-face appointment with their NSPS adviser and setting a quit date;

£50 if quit 4 weeks after their quit date corroborated by a carbon monoxide breath test result less than 10 ppm collected by a research nurse;

£100 if quit after 12 weeks corroborated by a carbon monoxide breath test collected by a research nurse;

£200 if they self report quit for at least 2 months when contacted for primary outcome assessment by the Helpline at 34 to 38 weeks gestation. This will be corroborated by a carbon monoxide breath test result less than 10 ppm collected by a research nurse.

### Trial participation payments

In order to minimize loss to follow-up, particularly among control participants, £25 will be given to all participants if they provide primary outcome information (and required samples to corroborate abstinence) at 34 and 38 weeks gestation.

### Quantitative data collection

#### *Primary outcome*

*Smoking status at 34 to 38 weeks gestation, towards the end of pregnancy*. Follow-up telephone contact will be attempted by NHS Smokefree Pregnancy Study Helpline at a random date between 34 and 38 weeks gestation allocated at the time of the initial randomization. A patient record check will be made by the NHS Smokefree Pregnancy Service administrator looking for stillbirth, miscarriage or patient death the week prior to the telephone contact at 34 to 38 weeks gestation. Miscarriage or stillbirth may not preclude a woman from receiving vouchers if they are in the intervention group.

Three attempts will be made to contact participants. If no contact is possible the participants will be followed up by the research nurse either by telephone or by a home visit after a contact detail check with the participant’s General Practitioner. If participants self report as non-smokers then a research nurse will make an appointment to collect urine and saliva for cotinine estimation (as well as a breath test for carbon monoxide to trigger the incentive payment).

If successful contact is made, the participant will be asked: ‘Have you smoked in the last 8 weeks?’ If yes ‘Have you smoked more than 5 cigarettes in that time?’ Self report will be corroborated by cotinine estimation on saliva and urine. Urine (cut-off 44.7 ng/ml) or saliva (cut-off 14.2 ng/ml) cotinine will be measured by ABS laboratories limited ([contact]).

The important aspect of the primary outcome for this phase II trial is the proportion of participants successfully followed up from the intervention but particularly the control group. If acceptable levels (about 90%) of participants can be successfully followed up with a similar proportion in the intervention and control groups, then individual randomization can be accepted as a design choice for a future phase III trial that does not produce significant bias due to differential loss to follow-up between groups.

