**Design and methods:**

This study is a phase II exploratory individually randomized controlled trial comparing standard care for pregnant smokers with standard care plus the additional offer of financial voucher incentives to engage with specialist cessation services and/or to quit smoking during pregnancy.

Participants (n = 600) will be pregnant smokers identified at maternity booking who, when contacted by specialist cessation services, agree to having their details passed to the NHS Smokefree Pregnancy Study Helpline to discuss the trial. The NHS Smokefree Pregnancy Study Helpline will be responsible for telephone consent and follow-up in late pregnancy. The primary outcome will be self reported smoking in late pregnancy verified by cotinine measurement. An economic evaluation will refine cost data collection and assess potential cost-effectiveness while qualitative research interviews with clients and health professionals will assess the level of acceptance of this form of incentive payment. The research questions are: What is the likely therapeutic efficacy? Are incentives potentially cost-effective? Is individual randomization an efficient trial design without introducing outcome bias? Can incentives be introduced in a way that is feasible and acceptable?

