## Background

Smoking during pregnancy increases miscarriage and stillbirth, accounting for up to 4000 UK deaths annually, and pre-term birth and low birth weight leading to perinatal morbidity [1]. A third of excess stillbirths and post-natal deaths associated with living in deprived areas are explained by smoking during pregnancy [2]. In Scotland 70% of women have a baby [3], making pregnancy an opportunity to help most women quit before their health is permanently compromised. In 2009, 24% of women booking for maternity care self-reported as current smokers [4]. Less than 1 in 20 of these women quit [5]. A study in the USA [6] in 2001 calculated the additional first year costs to health services as $1200 per smoker. Smoking is a major preventable cause of premature mortality for the mother, and lifelong benefits of quitting for children include reduced incidence of asthma and attention deficit disorder.

Following the 1998 White paper ‘Smoking Kills’, evidence-based National Health Service (NHS) smoking cessation services using behavioral support were developed [7-9] and now exist throughout Scotland [5]. Most of these services aim to provide tailored support (referred to in this paper as NHS Smokefree Pregnancy Services - NSPS) to pregnant women on a one-to-one basis, and evidence suggests that such interventions during pregnancy are effective [10]. Nicotine replacement therapy (NRT) is also offered, although its efficacy in pregnancy is not yet clear [10]. In Greater Glasgow & Clyde (GG&C), with 15,000 pregnancies per year, pregnant smokers identified at maternity booking are currently routinely referred to the NSPS on an ‘opt-out’ basis, without consent for transfer of contact information [7]. This practice is in keeping with the recent National Institute for health and Clinical Excellence (NICE) guidelines in the UK [11]. Women are then contacted by NSPS advisers who ask if they would like to quit and offer a face-to-face appointment in a clinic or home setting. If the client attends they set a quit date and a risk assessment for use of NRT during pregnancy is performed.

Participation figures for areas with recognized specialist smoking cessation in pregnancy services from a Scotland-wide audit are shown below [5]:

A. Estimated number of pregnant smokers at maternity booking [12], 8170 (100%).

B. Smokers identified by self report at routine booking questionnaire, 6128 (75%).

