### NHS Smokefree Pregnancy Services Greater Glasgow & Clyde Health Board area

At their maternity booking appointment pregnant women in NHS GG&C are asked for consent for screening which includes procedures to identify and offer treatment to current smokers – self report and routine carbon monoxide breath test with follow-up by NSPS. All women with either a carbon monoxide level of 5 ppm and above or self reported as current smokers (at least 1 cigarette in the last week) are notified to NSPS using a rapid electronic system. NSPS advisers contact these women by telephone and offer a smoking cessation counseling service which utilizes ‘Withdrawal Oriented Therapy’ [23]. Support includes a face-to-face appointment, weekly telephone support for 4 weeks and the offer of NRT dispensed by local pharmacies free of charge to support a quit attempt for up to 12 weeks.

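### The primary outcome is corroborated by cotinine alone while both arms are offered NRT, so a woman abstinent for 8 weeks but still on NRT can be counted as a smoker

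*Protocol article*

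**What the plan says.** The abstract of the protocol article defines the outcome: "The primary outcome will be self reported smoking in late pregnancy verified by cotinine measurement". The Primary outcome section repeats this ("Self report will be corroborated by cotinine estimation on saliva and urine") and fixes the thresholds: "Urine (cut-off 44.7 ng/ml) or saliva (cut-off 14.2 ng/ml) cotinine will be measured by ABS laboratories limited". The two outcome questions printed there concern cigarettes only: any smoking in the last 8 weeks and, if so, whether more than 5.

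The research nurse also takes a breath test when collecting samples from self-reported non-smokers. Its stated purpose is different: "as well as a breath test for carbon monoxide to trigger the incentive payment". Under Voucher incentive payments, the £200 late-pregnancy voucher depends on a self-report of at least 2 months' abstinence, and "This will be corroborated by a carbon monoxide breath test result less than 10 ppm collected by a research nurse".

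The section on the NHS Smokefree Pregnancy Services (NSPS) makes NRT part of standard care, hence available in both arms: "the offer of NRT dispensed by local pharmacies free of charge to support a quit attempt for up to 12 weeks". The Background says where NRT is considered: "If the client attends they set a quit date and a risk assessment for use of NRT during pregnancy is performed". The incentive arm receives £50 for attending that appointment and setting a quit date.

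**The concern.** Cotinine shows exposure to nicotine, whatever its source. This is general pharmacology and is not stated in the article. A rule that compares cotinine with a single cut-off therefore cannot separate a woman who smokes from one who has stopped and uses NRT. Applied as printed, the cut-offs contradict the second woman's truthful self-report.

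Two results are at stake. The first is the quit rate in each arm, and so the efficacy estimate that research question 1 asks for and that a phase III trial would use. The second is the incremental cost per late-pregnancy quitter. The voucher is paid on CO and the quit is counted on cotinine, so the same woman can add £200 to the cost and nothing to the number of quitters.

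A later analysis plan cannot repair this alone. If nicotine use is not asked about at the outcome contact, it is hard to recover afterwards.

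**Working it through.** **1. The plan's own figure.** Inputs from Sample size and Figure 2: 4% in usual care, 11.4% (90% power) or 10.2% (80% power) with incentives, 300 per arm, continuity-corrected χ² test, 5% level. The two-sided continuity-corrected formula gives 298 per arm (596 in all) and 300 per arm (600 in all). The plan's figures reproduce and are not in dispute. Power at 300 per arm for 4% against 11.4% is 90.3% by the formula, and 91.4% by exact enumeration of both binomial distributions under the same test. Exact values are used below.

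**2. Who can be affected.** Let T be the gestational week of the outcome contact (34 to 38) and Q the week of the quit date, taken as the start of NRT.
- A 12-week course still runs at T only if Q > T − 12.
- Eight weeks' abstinence at T requires Q ≤ T − 8.

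| T (weeks) | Q later than | Q no later than |
|---|---|---|
| 34 | 22 | 26 |
| 36 | 24 | 28 |
| 38 | 26 | 30 |

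For any one woman the range is about 4 weeks wide. It can be reached, since booking is allowed up to 24 weeks and the consent call comes at least 7 days after the first NSPS call. NRT use beyond the supplied course, or a repeat attempt, would add to it.

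**3. Effect on the result.** Let f be the share of true quitters who are cotinine-positive from NRT at T. Observed rate = true rate × (1 − f). The documents give no value for f, so the values below are assumptions. True rates are 4% and 11.4%, a difference of 7.4 points and a risk ratio (RR) of 11.4/4 = 2.85.

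| f control | f incentive | Observed rates | Difference (points) | RR | Exact power |
|---|---|---|---|---|---|
| 0 | 0 | 4.0% v 11.4% | 7.4 | 2.85 | 91% |
| 5% | 5% | 3.8% v 10.8% | 7.0 | 2.85 | 90% |
| 10% | 10% | 3.6% v 10.3% | 6.7 | 2.85 | 88% |
| 20% | 20% | 3.2% v 9.1% | 5.9 | 2.85 | 83% |
| 10% | 20% | 3.6% v 9.1% | 5.5 | 2.53 | 75% |
| 20% | 10% | 3.2% v 10.3% | 7.1 | 3.21 | 92% |

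In numbers of women at f = 10% in both arms: 300 × 0.04 × 0.10 = 1.2 in control and 300 × 0.114 × 0.10 = 3.4 in the incentive arm. The second count is larger because that arm has more quitters; with equal f, the risk ratio does not move.

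**4. Effect on the cost per quitter.** With equal f and unchanged costs, the incremental number of quitters is multiplied by (1 − f), so the incremental cost per quitter is multiplied by 1/(1 − f): 1.05, 1.11 and 1.25 at f = 5%, 10% and 20%.

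**5. The article's other markers.** Quitting at 4 weeks, a secondary outcome in both arms, is corroborated by CO at pharmacy visits for collecting NRT. The late voucher is also paid on CO. Only the primary outcome uses a marker that NRT itself raises.

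**The case against.** The strongest objection is that this is an omission from a condensed article. Nowhere does it say that a cotinine-positive abstainer on NRT counts as a smoker, and a rule for discordant results could sit in the full protocol, the case report form or the SAP. In part this stands: such a rule may exist. But the printed cut-offs give the wrong answer for this woman, the printed outcome questions cover cigarettes only, and CO is given a payment purpose that does not apply to controls. These are matters of data collection as well as analysis.

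Second, exposure is narrow, and the Sample size section says the trial is not designed to detect a specified difference. The Primary outcome section puts the weight on completeness of follow-up. This stands. Power here is only a scale for the size of the effect; the consequence lies in the efficacy and cost estimates carried forward.

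Third, strict cotinine is a defensible conservative choice, and the CO test carries £200 in the incentive arm. This also stands, and is why both results should be shown.

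A reader might infer that the error falls mainly on the incentive arm and biases the trial against incentives, because the £50 voucher rewards the appointment where NRT is assessed. With misclassification in that arm only, shares of 5%, 10% and 20% would give exact power of 87%, 82% and 67%. The documents do not support this reading. They report no NRT use by arm, they expect women in both arms to collect NRT at pharmacies, and higher attendance does not show that a larger share of quitters is on NRT at outcome.

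**Conclusion.** The point holds in a limited form. As printed, the primary outcome can count a woman abstinent for 8 weeks and still on NRT as a smoker, while the voucher rule can pay her as a quitter. The quit count and the cost per quitter are then inconsistent.

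The size depends on a share that the documents do not give. Equal shares of 5% to 20% in both arms take 0.4 to 1.5 points off the 7.4-point difference and leave the risk ratio alone. The loss is greater only if the share is higher in the incentive arm, which is plausible but undocumented; if it were higher among controls, the risk ratio would be overstated. The conclusion rests on cotinine responding to NRT, on NRT starting at the quit date, and on the cut-offs being applied as written.

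**What to change.** - At the outcome call and the sample visit, ask every self-reported abstainer in both arms about current use of NRT or other nicotine products.
- State that the CO reading at that visit is taken in both arms and recorded as outcome data, not only to trigger payment.
- Pre-specify an analysis that classifies self-reported abstainers on NRT by CO, with its cut-off fixed in advance; the article uses 5, 7 and 10 ppm for different purposes. Report it alongside the strict cotinine-only result, and name one of the two as primary before the data are seen.
- Carry both quit counts into the cost per quitter.

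The cost is one extra question and a short addition to the analysis plan. The article already has the nurse take CO from self-reported non-smokers. At the time of writing 199 of 600 women were enrolled, so women still to be enrolled could be covered. The downside is that CO has a shorter detection window than cotinine and, in the incentive arm, the same test triggers a payment. The CO-based result could therefore err in favor of incentives and should not be reported alone.
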